### Statistical Analysis

We calculate the sample size by comparing two independent samples. A *t*-test compares the mean uw-mRS at 90 days and corresponding two-sided 95% confidence intervals if the assumption of normality is not valid. Although the mRS is a primary endpoint, the difference among the uw-mRS categories is significant, and the *t*-test assumption and central limit theorem are probably met. The calculation of uw-mRS will be adjusted for baseline uw-mRS and baseline covariates associated with mRS in a linear regression model. Stratified analyses of the primary outcome and pooled measures are conducted by the Cochran–Mantel–Haenszel analyses and multiple ordinal regressions. We use a proportional odds model to process dichotomized outcomes of uw-mRS 0-1 vs. 2-6 with binary logistic regression. Participants in the intervention group who give up during the program will be excluded from the analysis. In addition, subjects in both treatment groups will be excluded from the protocol analysis if any violations of the following protocols after randomization and during intervention and follow-up. All analyses are performed by SPSS 27.0.

Besides, we explore the missing data and compare the distribution of critical variables. Suppose there is a reasonable amount of missing data and the data summary indicates that the data are missing at random. In that case, all analyses will be performed after multiple imputations of missing data using baseline variables as auxiliary variables.

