### Primary and Secondary Outcomes

The primary endpoint is the utility-weighted modified Rankin Scale (uw-mRS) at 90 days assessed with a telephone interview. Secondary endpoints include time-dependent phenomena such as the alarm to CT scan completed time, the alarm to treatment decision time, the alarm to thrombolytic time, quality of life assessed with EQ-5D at follow-ups over 5 years, symptomatic intracranial hemorrhage combined with NIHSS score, as well as cost-effectiveness.

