### Sample Size Estimation

Previous studies suggested that the difference in mean 90d uw-mRS between groups ranged from 0.024 to 0.25. However, according to our pilot study data, we anticipate that the difference in 90d mean uw-mRS is 0.09 (0.59 vs. 0.50) with a standard deviation of 0.5 in both groups. Considering a type-I error of 0.05, a study power of 0.8, and a two-sided test, we included a total sample size of 484 participants after considering a 10% dropout rate, each group with 242 participants.

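### The dichotomised outcome applies unweighted mRS category numbers (0–1 vs 2–6) to the utility-weighted score, and gives one binary outcome two model names

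*Protocol article*

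**What the plan says.** Three statements in the protocol article bear on this point.

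- **Primary and Secondary Outcomes:** "The primary endpoint is the utility-weighted modified Rankin Scale (uw-mRS) at 90 days".
- **Sample Size Estimation:** the investigators anticipate that "the difference in 90d mean uw-mRS is 0.09 (0.59 vs. 0.50"), "with a standard deviation of 0.5 in both groups". They also report that in earlier studies "the difference in mean 90d uw-mRS between groups ranged from 0.024 to 0.25". All of these are fractions of one unit.
- **Statistical Analysis:** "We use a proportional odds model to process dichotomized outcomes of uw-mRS 0-1 vs. 2-6 with binary logistic regression". The sentence just before it plans "Cochran–Mantel–Haenszel analyses and multiple ordinal regressions" for stratified analyses of the primary outcome and pooled measures.

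The same section calls the mRS a primary endpoint and speaks of categories of the uw-mRS, so it does not keep the two scales apart. The eligibility criteria under Participants use the mRS as a category number (below 3).

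**The concern.** The figures 0–1 and 2–6 together cover the seven integer grades of the unweighted mRS. Applied to a score with expected means near 0.55, they do not separate good from poor outcomes, because nearly everyone falls below the upper group. The direction may also change: a low mRS grade is a good outcome, whereas on a utility scale a high value is good. The second part of that is inferred from the name of the scale; the article does not state it.

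The model wording adds a smaller ambiguity. A proportional odds model is normally chosen for an outcome with three or more ordered levels, and binary logistic regression for one with two. With both names on one dichotomy, a reader cannot tell whether a single binary analysis is meant or whether a seven-level analysis has been merged into the sentence.

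What is at stake is one supportive analysis. An analysis plan that copies the sentence inherits an outcome with no usable contrast. One that quietly corrects it departs from the published protocol, and the correction may later look post hoc.

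**Working it through.** The article gives no figure for the dichotomised analysis, so there is none to reproduce. The check asks what the stated cut does on the stated scale.

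**Inputs.** Means 0.59 and 0.50, SD 0.5, 242 per group (Sample Size Estimation); cut 0–1 vs 2–6 (Statistical Analysis). The utility weights are not given, so results are shown under several assumptions.

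**Step 1: distance from the means to the upper group.** k = (2 − mean)/SD.
- (2 − 0.59)/0.5 = 2.82
- (2 − 0.50)/0.5 = 3.00

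**Step 2: share of patients at 2 or above.**

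| Assumption | Mean 0.59 | Mean 0.50 |
|---|---|---|
| No utility exceeds 1 | 0 of 242 | 0 of 242 |
| Normal approximation, 1 − Φ(k) | 0.24%, about 0.6 of 242 | 0.13%, about 0.3 of 242 |
| Any distribution (Cantelli), at most 1/(1 + k²) | 1/8.95 = 11.2% | 1/10 = 10.0% |

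The last row is a ceiling. It is reached only by a two-point distribution with one point exactly at 2, which is not a credible seven-grade utility score. The realistic reading is an empty or almost empty upper group.

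**Step 3: illustration.** mRS grades were simulated for 484 patients with assumed category probabilities and mapped to assumed equally spaced weights from 1 to 0. The mean utility was 0.594. All 484 fell in 0–1 and none in 2–6, so the outcome was constant and no odds ratio could be estimated.

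**Step 4: could another scaling rescue the wording?** A 0–10 scaling would need means near 5.9 and 5.0 and so does not match the article. In the simulation it would also have put 42 patients in 0–1, all of them at mRS 6, which is the reverse of a good-outcome group.

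**Step 5: the lower group.** If any weight were negative, those patients would fall in neither group; so would anyone with a value strictly between 1 and 2. The article's own figures do not establish a 0-to-1 range: on that range, a mean of 0.59 allows an SD of at most √(0.59 × 0.41) = 0.492, slightly below the stated 0.5. Complete membership of the 0–1 group is therefore conditional on the weights.

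**Step 6: the model names.** The proportional odds model is logit P(Y ≤ j) = α_j − βx with one β for all cuts j. With two levels there is one cut and one intercept, which is binary logistic regression. On the simulated mRS grades cut at 0–1 vs 2–6:

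| Model | Log odds ratio | SE |
|---|---|---|
| Binary logistic | 0.5545 | 0.1875 |
| Proportional odds, two levels | 0.5545 | 0.1875 |
| Proportional odds, seven levels | 0.508 | 0.161 |

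The first two are the same analysis. The third is a different one, so it matters whether it was intended.

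**The case against.** The strongest reply is that this is a slip of label that any analyst would see through. The digits match the mRS grades, the article uses mRS category numbers for eligibility, and once mRS is read for uw-mRS the threshold and direction are fixed in print. The dichotomy is not among the listed secondary endpoints, and nothing in the primary analysis depends on it. Most of this stands, and it limits the consequence. It does not make the sentence right: the error is in the operative analysis text, in a section that mixes the two scales more than once, so the intended scale has to be guessed.

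Three stronger readings are tempting, and the article does not support them.

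- *The analysis cannot be run because a proportional odds model is applied to a binary outcome.* It can be run; with two levels the model is logistic regression, and the sentence names logistic regression as well.
- *The ordinal analysis across all mRS grades would be lost.* The preceding sentence already plans "Cochran–Mantel–Haenszel analyses and multiple ordinal regressions". What is unclear is only whether the proportional odds label belongs there.
- *All patients in both arms would certainly fall in 0–1.* This needs every weight to lie between 0 and 1, and the weights are not given.

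The choice of covariates and a check of proportionality are details that an article commonly leaves to the full protocol or analysis plan. Their absence is not part of this point.

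**Conclusion.** The point holds as an error of scale in a stated analysis rule. On the article's own means and SD, the 2–6 group would be exactly empty if utilities do not exceed 1. Under a normal approximation it would hold fewer than one of 242 patients per arm. On no reading that fits the stated means does the sentence define the intended good-outcome group.

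The double model name is a mislabel. It does not block the fit, but it leaves open whether a seven-level analysis was also meant.

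A reader might infer that the trial's main result is at risk. It is not: the primary comparison is of mean uw-mRS at 90 days, and neither that estimate nor the data to be collected changes. The sentence should be corrected, but as a supportive-analysis matter.

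**What to change.** In the Statistical Analysis section, and in the analysis plan if it carries the same sentence:

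1. Define the dichotomised outcome as unweighted mRS 0–1 vs 2–6 at 90 days, analysed by binary logistic regression.
2. Move the proportional odds model to the ordinal regression already named in the preceding sentence, and state that its outcome is the ordinal mRS, grades 0 to 6.
3. Describe both as supportive of the primary difference in mean uw-mRS, and use mRS and uw-mRS consistently through the section.

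The cost is wording only. The mRS grade has to be recorded to derive the uw-mRS, so no new data are needed. Making the change before outcome data are examined avoids any appearance of a post-hoc choice.

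### The dichotomised 90-day analysis counts every mRS of 2 as unfavourable although entry admits mRS 2, so a full return to a pre-stroke mRS of 2 is grouped with grades 3 to 6 (supportive analysis only; minor)

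*Protocol article*

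**What the plan says.** Three statements in the protocol article bear on this.

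- **Participants.** The third inclusion criterion requires a candidate for t-PA whose mRS is below 3. Grades 0, 1 and 2 qualify. The criterion does not say whether the grade refers to the time before the stroke or to presentation.
- **Primary and Secondary Outcomes.** "The primary endpoint is the utility-weighted modified Rankin Scale (uw-mRS) at 90 days assessed with a telephone interview". No dichotomised mRS appears in the list of endpoints.
- **Statistical Analysis.** Besides the comparison of means and ordinal regressions, the section plans "dichotomized outcomes of uw-mRS 0-1 vs. 2-6 with binary logistic regression". The cut carries no exception for the entry grade. Baseline adjustment is attached to a different model: uw-mRS is to be "adjusted for baseline uw-mRS and baseline covariates associated with mRS in a linear regression model". No covariates are named for the logistic model. The Discussion says only in general terms that baseline parameters will be adjusted for.

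**The concern.** The set of grades allowed at entry is wider than the set counted as favourable at 90 days. Acute stroke care can hardly be expected to leave a patient less disabled than before the stroke. On the pre-stroke reading, a patient who enters from grade 2 therefore has almost no chance of a favourable score, however well treatment works. Such a patient contributes almost no information on treatment to the dichotomised analysis, and a complete recovery is reported in the same category as severe disability or death.

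At stake are the effect estimate, the power and the reported good-outcome rates of this one analysis. An unadjusted version would also move with any difference between arms in the share of patients at pre-stroke mRS 2. The Discussion concedes that selection by MSU availability is hard to avoid and may leave the arms unequal at baseline.

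**Working it through.** **1. Is there a figure to reproduce?** The plan gives no sample size, power or expected rates for the dichotomised analysis. Its total of 484 belongs to the comparison of means. Here 242 per arm serves only as a headcount, and nothing below depends on how it was derived.

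**2. The two rules side by side.** Entry set {0, 1, 2}; favourable set at 90 days {0, 1}. Three illustrative records, with the entry mRS read as pre-stroke:

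| Record | Pre-stroke mRS | 90-day mRS | Category under the printed cut |
|---|---|---|---|
| A | 0 | 1 | favourable, although one grade worse |
| B | 2 | 2 | unfavourable, although fully returned |
| C | 2 | 5 | unfavourable, the same as B |

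If the entry mRS is instead read as the grade at presentation, patients at 0 or 1 already start in the favourable category. The time point therefore matters on either reading.

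**3. Size under assumptions.** The documents give neither the share s of patients at pre-stroke mRS 2 nor the 90-day rates. Assumed:

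- Favourable rates of 40% (control) and 50% (MSU), counting return to the pre-stroke grade as favourable, in every stratum.
- No favourable outcomes under the printed cut among patients at pre-stroke mRS 2.
- s = 5%, 10% or 20%, that is about 24, 48 or 97 of 484 patients.
- n = 242 per arm, two-sided 0.05.

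*Unadjusted.* The rates become p0 = 0.40(1 − s) and p1 = 0.50(1 − s). Power = Φ(z − 1.96), with z = (p1 − p0) / √{[p0(1 − p0) + p1(1 − p1)] / n}. At s = 0: z = 0.10 / √[(0.24 + 0.25)/242] = 0.10/0.0450 = 2.22, so power = Φ(0.26), about 60%. At s = 20%: z = 0.08 / √[(0.2176 + 0.24)/242] = 0.08/0.0435 = 1.84, so power is about 45%.

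*Stratified on pre-stroke mRS.* A stratum without favourable outcomes drops out. The effect in the remaining patients stays at 40% vs 50%, with (1 − s) × 242 per arm. At s = 20%, n = 193.6: z = 0.10 / √(0.49/193.6) = 1.99, so power is about 51%.

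| s | Difference, unadjusted (points) | Power, unadjusted | Sample-size factor, unadjusted | Power, stratified | Sample-size factor, stratified |
|---|---|---|---|---|---|
| 0 | 10.0 | 60% | 1 | 60% | 1 |
| 5% | 9.5 | 56% | 1.10 | 58% | 1.05 |
| 10% | 9.0 | 53% | 1.20 | 56% | 1.11 |
| 20% | 8.0 | 45% | 1.46 | 51% | 1.25 |

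The unadjusted factor is [p0(1 − p0) + p1(1 − p1)]/(p1 − p0)² relative to s = 0; the stratified factor is 1/(1 − s). Using the pooled variance under the null lowers these powers by less than half a point.

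**4. Reported rates.** They are understated by 0.40s and 0.50s: 2.0 and 2.5 points at s = 5%, 4 and 5 at 10%, 8 and 10 at 20%.

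**5. Imbalance.** With no treatment effect and a common rate of 45%, a 5-point difference between arms in s gives an apparent difference of 0.45 × 5 = 2.25 points if unadjusted. Stratification removes this shift.

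**6. Effect of the fix.** If return to the pre-stroke grade counts as favourable, the assumed rates apply to everyone. The difference is then 10 points and power about 60% for every s.

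**The case against.** The strongest reply is that a fixed 0–1 cut is a coherent question: how many patients are free of meaningful disability at 90 days. It contradicts nothing else in the article, and the article never says that the cut is meant to measure recovery from the index stroke. It is one supportive analysis, and the trial was not sized on it. All of this stands, and it is why the plain split should be kept as a sensitivity analysis and why the point is minor.

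It can also be said that covariates for a supportive model are commonly left to a fuller document. That stands for the covariates, so their absence alone is no finding. The cut, however, is printed without an exception.

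Three stronger readings are tempting, and the documents do not support them:

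- *That the primary result is compromised.* The primary endpoint is mean uw-mRS. The ordinal analyses separate a 90-day grade of 2 from grades 3 to 6.
- *That the cut favours one arm.* It is identical in both. Under balanced allocation it dilutes the effect; only an unadjusted imbalance in pre-stroke mRS would shift it.
- *That covariate adjustment could not help.* Under the assumptions above, stratification restores the 10-point effect in the remaining patients, recovers part of the lost power and removes the imbalance shift. What it cannot do is rescore the patients who returned to grade 2 or recover their information.

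**Conclusion.** The point holds as a minor one. On the pre-stroke reading, the printed dichotomy groups a complete return to mRS 2 with grades 3 to 6, in both arms. The consequences stay within this supportive analysis: dilution, lower power, understated good-outcome rates and, without adjustment, sensitivity to baseline imbalance.

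The size cannot be computed from the documents. For 5 to 20% of patients at pre-stroke mRS 2, power falls by about 4 to 15 percentage points unadjusted, or about 2 to 9 when stratified. Those figures rest on the assumed 40% vs 50%, on the same effect in every stratum and on no favourable outcomes in the affected stratum. At the low end of the range the loss is small.

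**What to change.** In Statistical Analysis:

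- Define the dichotomy on the unweighted mRS as 0–1 at 90 days, or return to the pre-stroke mRS, versus all other outcomes. The grades 0 to 6 in the printed cut are mRS grades, not utilities.
- Adjust the logistic model for pre-stroke mRS.
- Keep the plain 0–1 versus 2–6 split as a sensitivity analysis.

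In Participants, state the time point to which the entry mRS refers.

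The cost is a few sentences. An mRS is already needed for eligibility and a baseline value for the linear model, so no data item is added if these refer to the pre-stroke state. The downsides are slightly less direct comparability with trials that report plain mRS 0–1, which the sensitivity analysis covers, and reliance on a recalled pre-stroke mRS. The change should be fixed before the 90-day results are analysed, so that it cannot look data-driven.

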### Participants

A total of 484 participants are recruited from the Ya’an people’s Hospital, 242 of whom were randomized to the intervention group and the rest randomized to the comparison group.

Each participant must meet all of the inclusion criteria to be enrolled in this study, which are given as follows:

1.Patients need to be aged over 18 years, with a final diagnosis of ischemic stroke.2.Patients’ confirmed onset-to-alarm time is less than 4.5 h.3.Patient is recognized as a t-PA candidate, with mRS scores less than 3.4.Patients volunteer to participate and sign an informed consent.

The exclusion criteria include uncertain symptom onset, no focal stroke-like symptoms, severe malignant, or pregnancy.

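### Participants who give up are excluded from the analysis in the MSU group only, with no matching rule for regular care and no analysis of all randomised patients stated

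*Protocol article*

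**What the plan says.** The Participants section describes a 1:1 randomised comparison of 484 patients, "242 of whom were randomized to the intervention group and the rest randomized to the comparison group". The Primary and Secondary Outcomes section fixes the endpoint: "The primary endpoint is the utility-weighted modified Rankin Scale (uw-mRS) at 90 days assessed with a telephone interview".

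Three statements in the Statistical Analysis section decide who is analysed:

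- On giving up: "Participants in the intervention group who give up during the program will be excluded from the analysis". Only the intervention group is named.
- On protocol violations, in the next sentence and introduced as an addition: "subjects in both treatment groups will be excluded from the protocol analysis if any violations of the following protocols after randomization". This names both groups.
- On missing data, provided that the amount is reasonable and the data appear missing at random: "all analyses will be performed after multiple imputations of missing data using baseline variables as auxiliary variables".

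Nowhere does the article state an intention-to-treat analysis or any other analysis of all randomised patients. It does not say what giving up means, or how regular-care patients who give up are handled.

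**The concern.** Randomisation makes the two groups comparable only as long as the groups analysed are the groups allocated. Giving up is a post-allocation event that may be related to prognosis, to the course of the stroke or to the care received. Removing patients for that reason from one group leaves a selected MSU group compared with a regular-care group to which no such selection is stated to apply. Baseline adjustment, which the article offers against bias in general, cannot be relied on to repair selection on a later event.

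The primary result is at stake: the estimated difference in mean uw-mRS and its type I error. The rule also fits the question poorly. The Study Design section calls the trial pragmatic and asks whether deploying the MSU improves function, and patients who leave the MSU pathway are part of what deployment delivers.

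An article may leave analysis sets to a fuller document, and silence on them would be no finding. Here a specific rule is stated, and it names one group.

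**Working it through.** **Reading the rules side by side.** The sentence on giving up and the sentence on violations differ in three respects: the event (giving up; protocol violation), the groups named (intervention only; both) and the analysis named (the analysis, without qualification; the protocol analysis). The literal reading is therefore two separate rules, the first of which applies to the analysis generally, including the primary comparison.

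**Inputs from the document.** The Sample Size Estimation section gives the planned effect and SD, "the difference in 90d mean uw-mRS is 0.09 (0.59 vs. 0.50) with a standard deviation of 0.5 in both groups", and the numbers and dropout rate, "we included a total sample size of 484 participants after considering a 10% dropout rate, each group with 242 participants".

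**The plan's own figure.** With "Considering a type-I error of 0.05, a study power of 0.8, and a two-sided test", the usual two-sample formula gives n per group = 2 × (1.960 + 0.842)² × 0.5² / 0.09² = 484.5, so 485 per group and 970 in total before dropout. The stated total of 484 is not reproduced. That is a separate matter. The check below uses 242 only as the number randomised to each group.

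**Assumptions, not in the document.**

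- There is no true effect: both groups have a true mean uw-mRS of 0.50.
- A share p = 0.10 of the MSU group gives up. This borrows the plan's overall dropout rate, which is not a rate of giving up in the MSU group.
- The excluded patients' true mean is m, which is varied.
- All 242 regular-care patients are analysed.
- The SD stays at 0.5 after exclusion.

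**Formulas.**

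- Bias = (0.50 - p·m)/(1 - p) - 0.50
- SE = 0.5 × √(1/(242(1 - p)) + 1/242)
- Type I error = P(|Z + bias/SE| > 1.96)

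With p = 0.10, the MSU number analysed is 242 × 0.9 = 217.8 and SE = 0.5 × √(1/217.8 + 1/242) = 0.0467.

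| Mean of excluded (m) | Calculation | Bias | Bias/SE | Share of 0.09 | Type I error |
|---|---|---|---|---|---|
| 0.2 | 0.48/0.9 - 0.50 | +0.033 | +0.71 | 37% | 11% |
| 0.3 | 0.47/0.9 - 0.50 | +0.022 | +0.48 | 25% | 7.6% |
| 0.5 | 0.45/0.9 - 0.50 | 0 | 0 | 0% | 5% |
| 0.7 | 0.43/0.9 - 0.50 | -0.022 | -0.48 | 25%, against MSU | 7.6% |

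The last error rate follows by symmetry from the row for 0.3. The excess false positives then point against the MSU.

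**Cross-check.** The bias also equals p × g, where g is the gap between completers and those who give up. For m = 0.3, completers average 0.522, so g = 0.222 and p × g = 0.022, as above. For p = 0.10 and an assumed g of 0.1 to 0.5, the absolute bias is 0.01 to 0.05, or 11% to 56% of 0.09. The sign is that of g.

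**The case against.** The strongest reply is that the two exclusion sentences together define a per-protocol set, giving up first and violations second, and that condensing the article blurred this. The reading is possible, so it is not proven that the one-group rule governs the primary analysis. It is less literal, however, because the second sentence changes the event, the groups and the name of the analysis. It also does not cure the problem, since a per-protocol set that drops those who give up from one group only is itself asymmetric.

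A reader might infer more than the document supports:

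- **That regular-care patients who give up stay in.** The article states no rule for them. The program may even mean the MSU programme, which a regular-care patient cannot give up. What can be said is that no matching rule is stated.
- **That the rule contradicts the imputation plan.** Imputation is conditional, and excluding some patients and imputing for the rest would be internally consistent. The two rules are unreconciled, not contradictory.
- **That the rule favours the MSU.** The document gives no outcomes for those who give up. If they do better than completers, for instance because mild deficits resolve, the bias runs against the MSU.

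Two further objections stand in part. If giving up means withdrawn consent or loss to follow-up, the outcome is missing anyway, and imputation from baseline variables under a missing-at-random assumption would not necessarily remove the bias. The fix therefore needs a sensitivity analysis. Also, eligibility depends on a final diagnosis of ischaemic stroke and on t-PA candidacy, so the wording should make clear who counts as randomised. That is a question of eligibility and does not justify a one-group exclusion.

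**Conclusion.** The rule is wrong as written and should be changed before analysis. It excludes randomised patients for an undefined post-allocation event in the MSU group only, beside no stated analysis of all randomised patients. That much is certain from the text. That it governs the primary comparison is the literal and more likely reading, not an established fact.

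The consequence is possible bias of unknown size and direction. In the scenarios worked out from an assumed 10% exclusion, it runs from -0.022 to +0.033 against a planned difference of 0.09, with type I error of up to 11% in place of 5%. It vanishes if giving up is unrelated to outcome. These figures rest on assumed outcomes and an assumed share of patients giving up. They show what the rule could do and do not predict what it will do. Its validity would depend on an assumption about those who give up that analysing everyone as allocated makes unnecessary wherever their outcomes are obtained.

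**What to change.** Replace the sentence on giving up with text to this effect:

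- The primary analysis includes all randomised participants in both groups, in the group to which they were allocated, whatever care they received or stopped. State who counts as randomised.
- Follow-up for the 90-day mRS continues after a participant leaves the programme, unless consent for follow-up is withdrawn.
- Missing outcomes are handled by the same rule in both groups, with a sensitivity analysis for outcomes not missing at random.
- Giving up is defined. Exclusions for giving up or for protocol violation apply identically to both groups and serve a per-protocol sensitivity analysis only.

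The cost is protocol or SAP wording and some follow-up calls, which are feasible because the primary endpoint is collected by telephone. The estimated effect may change in either direction.
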